## 6 ADVERSE EVENTS

An *Adverse Event (AE)* is defined as any new untoward medical occurrence or worsening of a preexisting medical condition in a clinical investigation subject administered study drug and that does not necessarily have a causal relationship with this treatment. An AE can therefore be any unfavorable and unintended sign (such as an abnormal laboratory finding), symptom, or disease temporally associated with the use of study drug, whether or not considered related to the study drug.

The causal relationship to study drug is determined by a physician and should be used to assess all adverse events (AE). The causal relationship can be one of the following:

Related: There is a reasonable causal relationship between study drug administration and the AE.

Not related: There is not a reasonable causal relationship between study drug administration and the AE.

The term "reasonable causal relationship" means there is evidence to suggest a causal relationship.

Adverse events can be spontaneously reported or elicited during open-ended questioning, examination, or evaluation of a subject. (In order to prevent reporting bias, subjects should not be questioned regarding the specific occurrence of one or more AEs).

### 6.1 Serious Adverse Events

A *Serious Adverse Event (SAE)* is any untoward medical occurrence that at any dose:

- results in death
- is life-threatening (defined as an event in which the subject was at risk of death at the time of the event; it does not refer to an event which hypothetically might have caused death if it were more severe)
- requires inpatient hospitalization or causes prolongation of existing hospitalization (see **NOTE** below)
- results in persistent or significant disability/incapacity
- is a congenital anomaly/birth defect
- is an important medical event (defined as a medical event(s) that may not be immediately life-threatening or result in death or hospitalization but, based upon appropriate medical and

scientific judgment, may jeopardize the subject or may require intervention [eg, medical, surgical] to prevent one of the other serious outcomes listed in the definition above). Examples of such events include, but are not limited to, intensive treatment in an emergency room or at home for allergic bronchospasm; blood dyscrasias or convulsions that do not result in hospitalization). Potential drug induced liver injury (DILI) is also considered an important medical event. (See [Section 6.6](#) for the definition of potential DILI.)

Suspected transmission of an infectious agent (eg, pathogenic or nonpathogenic) via the study drug is an SAE.

Although pregnancy, overdose, cancer, and potential drug induced liver injury (DILI) are not always serious by regulatory definition, these events must be handled as SAEs. (See Section 6.1.1 for reporting pregnancies).

**NOTE:**

The following hospitalizations are not considered SAEs in BMS clinical studies:

- a visit to the emergency room or other hospital department < 24 hours, that does not result in admission (unless considered an important medical or life-threatening event)
- elective surgery, planned prior to signing consent
- admissions as per protocol for a planned medical/surgical procedure
- routine health assessment requiring admission for baseline/trending of health status (eg, routine colonoscopy)
- medical/surgical admission other than to remedy ill health and planned prior to entry into the study. Appropriate documentation is required in these cases
- admission encountered for another life circumstance that carries no bearing on health status and requires no medical/surgical intervention (eg, lack of housing, economic inadequacy, caregiver respite, family circumstances, administrative reason)
- Admission for administration of anticancer therapy in the absence of any other SAEs (applies to oncology protocols)

### **6.1.1      *Serious Adverse Event Collection and Reporting***

Sections 5.6.1 and 5.6.2 in the Investigator Brochure (IB) represent the Reference Safety Information to determine expectedness of serious adverse events for expedited reporting. Following the subject's written consent to participate in the study, all SAEs, whether related or not related to study drug, must be collected, including those thought to be associated with protocol-specified procedures. All SAEs must be collected that occur during the screening period and within 30 days of discontinuation of dosing.

The investigator should report any SAE that occurs after these time periods and that is believed to be related to study drug or protocol-specified procedure.

An SAE report should be completed for any event where doubt exists regarding its seriousness.

If the investigator believes that an SAE is not related to study drug, but is potentially related to the conditions of the study (such as withdrawal of previous therapy or a complication of a study procedure), the relationship should be specified in the narrative section of the SAE Report Form.

SAEs, whether related or not related to study drug, and pregnancies, must be reported to BMS (or designee) within 24 hours. SAEs must be recorded on the SAE Report Form; pregnancies on a Pregnancy Surveillance Form (electronic or paper forms). The preferred method for SAE data reporting collection is through the eCRF. The paper SAE/pregnancy surveillance forms are only intended as a back-up option when the eCRF system is not functioning. In this case, the paper forms are to be transmitted via email or confirmed facsimile (fax) transmission to:

**SAE Email Address:** Refer to Contact Information list.

**SAE Facsimile Number:** Refer to Contact Information list.

For studies capturing SAEs through electronic data capture (EDC), electronic submission is the required method for reporting. The paper forms should be used and submitted immediately, only in the event the electronic system is unavailable for transmission. When paper forms are used, the original paper forms are to remain on site.

**SAE Telephone Contact** (required for SAE and pregnancy reporting): Refer to Contact Information list.

If only limited information is initially available, follow-up reports are required. (Note: Follow-up SAE reports should include the same investigator term(s) initially reported.)

If an ongoing SAE changes in its intensity or relationship to study drug or if new information becomes available, a follow-up SAE report should be sent within 24 hours to the BMS (or designee) using the same procedure used for transmitting the initial SAE report.

All SAEs should be followed to resolution or stabilization.

## **6.2 Nonserious Adverse Events**

A *nonserious adverse event* is an AE not classified as serious.

### **6.2.1 Nonserious Adverse Event Collection and Reporting**

The collection of nonserious AE information should begin at initiation of study drug. Nonserious AE information should also be collected from the start of a placebo lead-in period or other observational period intended to establish a baseline status for the subjects.

Nonserious AEs should be followed to resolution or stabilization, or reported as SAEs if they become serious (see [Section 6.1.1](#)). Follow-up is also required for nonserious AEs that cause interruption or discontinuation of study drug and for those present at the end of study treatment as appropriate. All identified nonserious AEs must be recorded and described on the nonserious AE page of the CRF (paper or electronic).

Completion of supplemental CRFs may be requested for AEs and/or laboratory abnormalities that are reported/identified during the course of the study.

### **6.3 Laboratory Test Result Abnormalities**

The following laboratory test result abnormalities should be captured on the nonserious AE CRF page or SAE Report Form (paper or electronic) as appropriate:

- Any laboratory test result that is clinically significant or meets the definition of an SAE
- Any laboratory test result abnormality that required the subject to have study drug discontinued or interrupted
- Any laboratory test result abnormality that required the subject to receive specific corrective therapy

It is expected that wherever possible, the clinical rather than laboratory term would be used by the reporting investigator (eg, anemia versus low hemoglobin value).

### **6.4 Pregnancy**

If, following initiation of the study drug, it is subsequently discovered that a study subject is pregnant or may have been pregnant at the time of study exposure, including during at least 5 half lives after product administration, the investigator must immediately notify the BMS Medical Monitor/designee of this event and complete and forward a Pregnancy Surveillance Form to BMS Designee within 24 hours and in accordance with SAE reporting procedures described in [Section 6.1.1](#).

The study drug will be permanently discontinued in an appropriate manner (eg, dose tapering if necessary for subject safety).

Protocol-required procedures for study discontinuation and follow-up must be performed on the subject unless contraindicated by pregnancy (eg, x-ray studies). Other appropriate pregnancy follow-up procedures should be considered if indicated.

Follow-up information regarding the course of the pregnancy, including perinatal and neonatal outcome and, where applicable, offspring information must be reported on the Pregnancy Surveillance Form.

Any pregnancy that occurs in a female partner of a male study participant should be reported to BMS. Information on this pregnancy will be collected on the Pregnancy Surveillance Form.

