### 3.5 Discontinuation of Subjects following any Treatment with Study Drug

Subjects MUST discontinue investigational product (and non-investigational product at the discretion of the investigator) for any of the following reasons:

- Subject's request to stop study treatment
- Any clinical adverse event (AE), laboratory abnormality or intercurrent illness which, in the opinion of the investigator, indicates that continued participation in the study is not in the best interest of the subject
- Termination of the study by Bristol-Myers Squibb (BMS)
- Loss of ability to freely provide consent through imprisonment or involuntarily incarceration for treatment of either a psychiatric or physical (eg, infectious disease) illness
- Pregnancy (subjects should be discontinued in an appropriate manner)
- Unblinding a subject for any reason (emergency or non-emergency)
- Repeat non-adherence by the subject with the requirements of the protocol or treatment (as determined by Investigator in consultation with the BMS Medical Monitor)
- Evidence of Hepatitis B or C infection
- Confirmed plasma HIV-1 RNA  $\geq 1000$  c/mL after Week 24
- Confirmed plasma HIV-1 RNA  $\geq 200$  c/mL after Week 48
- Emergence of genotypic and/or phenotypic resistance to any component of the study treatment regimen at any time after Screening
- Subject requires switching to any other ARV
- Development of pDILI (potential drug induced liver injury)
- Confirmed QTcB or QTcF value  $> 500$  msec
- Confirmed second degree (Type II) or third degree AV block at any time during the study
- New onset of serious mental illness or suicidal ideation that in the opinion of the investigators makes continuation in the study not in the best interest of the subject

All subjects who discontinue study drug should comply with protocol specified follow-up procedures as outlined in [Section 5](#) (ie, perform an Early Termination [ET] visit). The only exception to this requirement is when a subject withdraws consent for all study procedures including post-treatment study follow-up (no such period exists in this study) or loses the ability to consent freely (ie, is imprisoned or involuntarily incarcerated for the treatment of either a psychiatric or physical illness).

If study drug is discontinued prior to the subject's completion of the study, the reason for the discontinuation must be documented in the subject's medical records and entered on the appropriate case report form (CRF) page.

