## 4 STUDY DRUG

Study drug includes both Investigational [Medicinal] Product (IP/IMP) and Non-investigational [Medicinal] Product (Non-IP/Non-IMP) and can consist of the following:

| Table 4-1: Study Drugs for AI468038:        |                     |                      |                              |                                                                              |                                                                                      |
|----------------------------------------------------|---------------------|----------------------|------------------------------|------------------------------------------------------------------------------|--------------------------------------------------------------------------------------|
| Product Description / Class and Dosage Form | Potency      | IMP / Non-IMP | Blinded or Open Label | Packaging/ Appearance                                                 | Storage Conditions (per label)                                                |
| BMS-955176                                         | 60 mg a  | IMP                  | Blinded                      | Bottle/
A white to off-white, biconvex, oval shaped film coated tablet    | Store at 15 - 25°C

Protect from light.
Store in a tightly closed container |
| BMS-955176                                         | 120 mg a | IMP                  | Blinded                      | Bottle/
A white to off-white, biconvex, capsule shaped film coated tablet | Store at 15 - 25°C

Protect from light.
Store in a tightly closed container |
| Placebo to match
BMS-955176 60 mg a  | N/A                 | IMP                  | Blinded                      | Bottle/
A white to off-white, biconvex, oval shaped film coated tablet    | Store at 15 - 25°C

Protect from light.
Store in a tightly closed container |
| Placebo to match
BMS-955176 120 mg a | N/A                 | IMP                  | Blinded                      | Bottle/
A white to off-white, biconvex, capsule shaped film coated tablet | Store at 15 - 25°C

Protect from light.
Store in a tightly closed container |

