#### **4.1 Investigational Product**

An investigational product, also known as investigational medicinal product in some regions, is defined a pharmaceutical form of an active substance or placebo being tested or used as a reference in a clinical study, including products already with a marketing authorization but used or assembled (formulated or packaged) differently than the authorized form, or used for an unauthorized indication, or when used to gain further information about the authorized form.

The investigational product should be stored in a secure area according to local regulations. It is the responsibility of the investigator to ensure that investigational product is only dispensed to study subjects. The investigational product must be dispensed only from official study sites by authorized personnel according to local regulations.

In this protocol, investigational product(s) is/are: BMS-955176 and EFV. These products will be supplied.

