#### **4.2 Non-investigational Product**

Other medications used as support or escape medication for preventative, diagnostic, or therapeutic reasons, as components of the standard of care for a given diagnosis, may be considered as non-investigational products.

In this protocol, noninvestigational product(s) is/are: TDF/FTC. This product will be supplied.

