#### **4.5.2 Dose Modifications**

No dose adjustments or changes in intake frequency are allowed for any of the assigned study drugs in the protocol, except in the event of treatment-limiting renal toxicity, dose interval adjustments for TDF/FTC are permitted according to the local package insert/label, and only after the completion of the Week 2 Intensive PK optional Visit, if the subject is inclined to participate.

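### For a pregnant subject, Section 6.4 as defined makes stopping TDF/FTC mandatory, Section 3.5 makes it discretionary, and neither says which governs

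*Protocol*

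**What the plan says.** Two passages of the Protocol instruct sites on what to do with treatment when a subject is pregnant.

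- **Section 6.4 (Pregnancy):** "The study drug will be permanently discontinued in an appropriate manner (eg, dose tapering if necessary for subject safety". No product is named and the term carries no qualifier.
- **Section 3.5 (Discontinuation):** "Subjects MUST discontinue investigational product (and non-investigational product at the discretion of the investigator) for any of the following reasons". Pregnancy is one of the 16 reasons listed under that sentence.

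The product terms are defined in Section 4: "Study drug includes both Investigational [Medicinal] Product (IP/IMP) and Non-investigational [Medicinal] Product (Non-IP/Non-IMP"). The synopsis has the same definition. Section 4.1 states "In this protocol, investigational product(s) is/are: BMS-955176 and EFV", and Section 4.2 states "In this protocol, noninvestigational product(s) is/are: TDF/FTC".

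On changes of dose, Section 4.5.2 states "No dose adjustments or changes in intake frequency are allowed for any of the assigned study drugs in the protocol". Its one exception is a change in the TDF/FTC dosing interval for treatment-limiting renal toxicity.

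**The concern.** Sections 3.5 and 6.4 are both operative instructions for the same event, and on the protocol's own definitions they differ on whether the TDF/FTC backbone has to stop. Under one reading the investigator has no choice; under the other the choice is the investigator's. Two sites could handle two such subjects differently and each point to the protocol for support.

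Pregnancy is not a marginal event for this product. Section 1.5 gives developmental toxicity as one of two potential risks from the preclinical toxicology, and Section 6.1 requires pregnancies to be handled as SAEs. Section 1.1 counts viral suppression and prevention of transmission among the goals of therapy. An instruction on which antiretrovirals stop in this setting should have only one reading.

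The second, weaker question is whether the tapering that Section 6.4 offers as an example is compatible with the bar on dose adjustments in Section 4.5.2.

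**Working it through.** No arithmetic applies, since the point rests on no rate, sample size or error level. The check is a comparison of the passages.

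**Step 1. What Section 6.4 covers.** Study drug (Section 4) = investigational product + non-investigational product. Investigational product (Section 4.1) = BMS-955176 and EFV. Non-investigational product (Section 4.2) = TDF/FTC. Substituted into Section 6.4, permanent discontinuation covers TDF/FTC.

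**Step 2. What Section 3.5 covers.** For the same event, investigational product must stop and TDF/FTC is left to the investigator.

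| | Investigational product | TDF/FTC |
|---|---|---|
| Section 3.5 | must stop | investigator's discretion |
| Section 6.4, with the Section 4 definition | must stop | must stop |

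The sections agree on the first column and differ on the second. Neither states precedence.

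**Step 3. Whether usage elsewhere settles the meaning.** It does not; it points both ways.

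- Wide sense: inclusion criterion 2d (Section 3.3.1) counts EFV, TDF and FTC as study drugs, and Section 4.5.2 treats TDF/FTC as one of the assigned study drugs.
- Narrow sense: the contraception criteria in Section 3.3.1 attach the term to BMS-955176, and Section 5.5.1 sets the blinded study drug beside TDF/FTC. Both uses carry a qualifier.
- Narrow sense without a qualifier: after separating the two product classes, Section 3.5 itself speaks of subjects who discontinue study drug, meaning everyone who stops under its list, including those whose TDF/FTC continues.

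**Step 4. Tapering.** Section 4.5.2 has a single exception, which mentions neither pregnancy nor the ending of treatment. Taken literally, it leaves no room for the tapering in Section 6.4. It does not say, however, whether it governs the ending of treatment or only ongoing dosing.

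**Step 5. Size of the difference for one subject.** By Section 3.1.2 each arm has exactly one active investigational drug (BMS-955176 at one of three doses, or EFV) plus the TDF/FTC combination. The two readings therefore differ by TDF/FTC alone: one active investigational drug stopped, or that drug plus TDF/FTC. Table 5.1-2 notes that nothing is dispensed at Week 96 or early termination, so any TDF/FTC from study supply after that visit is limited to what the subject already holds.

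**The case against.** The strongest reply is that both sections can be obeyed at once. Stopping TDF/FTC is within the discretion that Section 3.5 gives, so a site that follows Section 6.4 literally never breaches Section 3.5, and Section 6.4 can be seen as the specific rule for pregnancy. Moreover, Section 3.5 uses study drug as shorthand for whatever is stopped under its list, so Section 6.4 may have been meant for the investigational product only. This softens the conflict but does not remove it. An investigator who continues TDF/FTC under Section 3.5 departs from Section 6.4 as defined, and the explicit definition in Section 4 still stands with no stated precedence.

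On tapering, the reply is largely right. Section 4.5.2 can fairly be read as a rule for ongoing dosing, and Section 6.4 offers tapering only as an example, where needed for safety. What remains is an unstated relation between the two sections. It is too strong to say that one forbids what the other permits.

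A reader might also infer three stronger consequences. The protocol does not support them.

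- *That a pregnant subject is left without antiretroviral treatment.* Nothing in Section 6.4 bars marketed therapy once study drug has stopped, so the end of study drug is not the end of treatment.
- *That safety follow-up of an exposed pregnancy is compromised because the SAE period, "within 30 days of discontinuation of dosing" (Section 6.1.1), would start on a different day.* Section 6.4 requires the course and outcome of the pregnancy, including the newborn, to be reported without that limit. Section 3.6 provides for follow-up to resolution of a pregnancy or SAE, and Section 6.1.1 keeps later SAEs believed related to study drug reportable. With no dispensing at early termination, any shift is bounded by drug already in hand.
- *That the readings differ by two or more investigational drugs.* Each arm has only one active investigational drug.

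**Conclusion.** The inconsistency is real and follows from the protocol's own definitions: for pregnancy, stopping TDF/FTC is mandatory under Section 6.4 as defined and discretionary under Section 3.5, with no stated precedence. The tapering point is secondary and amounts to a gap in wording. The conclusion assumes that a site applies the Section 4 definition to an unqualified use of the term in Section 6.4. The loose usage elsewhere makes the other reading possible, and that is itself the difficulty.

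The practical size is small. The subjects concerned are likely few, though the protocol gives no pregnancy rate from which to estimate a number. For each of them the readings differ by TDF/FTC only, and mainly by supply already dispensed. No effect on an endpoint or analysis has been shown. The case for acting is that these are direct instructions to sites on a safety event and that correcting them costs very little.

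**What to change.** Reconcile Sections 3.5, 6.4 and 4.5.2.

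1. Use the same product terms in both pregnancy passages, naming investigational product and TDF/FTC separately, so that Sections 3.5 and 6.4 give one instruction for each.
2. State whether the tapering mentioned in Section 6.4 is an exception to Section 4.5.2, or that Section 4.5.2 does not apply when treatment is being ended.

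Which drugs stop in pregnancy, and how, is a clinical decision for the sponsor; this point takes no view on it. The cost is a wording clarification in the protocol, with no added procedures, data or analyses.
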